## Abstract

**Background:**

Esophageal resection is associated with a high incidence of postoperative pneumonia. Respiratory complications account for almost half of the readmissions to the critical care unit. Postoperative complications can result in prolonged hospital stay and consequently increase healthcare costs. In cardiac surgery a preoperative inspiratory muscle training program has shown to prevent postoperative pneumonia and reduce length of hospital stay. While in some surgical centers inspiratory muscle training is already used in the preoperative phase in patients undergoing esophageal resection, the added value of this intervention on the reduction of pulmonary complications has not yet been investigated in large surgical populations other than cardiac surgery in a randomized and controlled study design.

**Methods/Design:**

The effect of a preoperative inspiratory muscle training program on the incidence of postoperative pneumonia in patients undergoing esophageal resection will be studied in a single blind multicenter randomized controlled trial (the PREPARE study). In total 248 patients (age >18 years) undergoing esophageal resection for esophageal cancer will be included in this study. They are randomized to either usual care or usual care with an additional inspiratory muscle training intervention according to a high-intensity protocol which is performed with a tapered flow resistive inspiratory loading device. Patients have to complete 30 dynamic inspiratory efforts twice daily for 7 days a week until surgery with a minimum of 2 weeks. The starting training load will be aimed to be 60% of maximal inspiratory pressure and will be increased based on the rate of perceived exertion.

The main study endpoint is the incidence of postoperative pneumonia. Secondary objectives are to evaluate the effect of preoperative inspiratory muscle training on length of hospital stay, duration of mechanical ventilation, incidence of other postoperative (pulmonary) complications, quality of life, and on postoperative respiratory muscle function and lung function.

**Discussion:**

The PREPARE study is the first multicenter randomized controlled trial to evaluate the hypothesis that preoperative inspiratory muscle training leads to decreased pulmonary complications in patients undergoing esophageal resection.

**Trial registration:**

NCT01893008.

## Background

The numbers of esophageal cancer patients are increasing worldwide. The incidence of esophageal cancer is increased by 50% in the past two decades [1]. Surgical resection, mostly preceded by neoadjuvant chemoradiotherapy, is regarded the only curable option for esophageal cancer [2]. While the in-hospital mortality rate is below 5% after this surgery, several studies report in-hospital postoperative pneumonia rates around 30% [2-4]. Respiratory complications account for almost half of the readmissions to critical care units [5] and the development of pneumonia is associated with a mortality of 20% compared with 3% among patients free of pneumonia [6]. Besides increased mortality, the high rate of pneumonia results in increased length of stay in the intensive care unit (ICU) and in the hospital [7,8] which results in increased and prolonged use of medical care, with subsequent consequences for healthcare costs. Therefore, preventing pneumonia is better than curing pneumonia.

Several factors associated with esophageal resection, such as diaphragmatic dysfunction as a result of intra-thoracic manipulation of tissue, perioperative lung collapse, mechanical ventilation, and supine positioning, can increase perioperative ventilatory demand [9]. When the ventilatory demand (or workload) exceeds the ventilatory capacity (or ability), this imbalance can lead to ventilatory pump failure. Following, ventilatory pump failure can result in alveolar hypoventilation which may progress to respiratory failure, pneumonia, or even death [9].

Physical therapy interventions to prevent pneumonia and other postoperative pulmonary complications (PPCs) often focus on postoperative prophylaxis using various respiratory techniques and devices [10-12]. A relatively new physical therapy intervention to prevent PPCs and pneumonia is preoperative inspiratory muscle training (IMT). IMT is performed with an inspiratory loading device and results in increased strength and endurance of the inspiratory muscles [13-15]. Since the ventilatory capacity partly depends on optimal respiratory muscle performance, increased inspiratory muscle function may lead to improved ventilatory capacity [9]. The hypothesis is that when IMT is applied in the preoperative phase of esophageal resection it may prevent the imbalance between ventilatory demand and ventilatory capacity resulting in a reduction of PPCs.

A large randomized controlled trial (RCT) found that IMT before coronary bypass surgery significantly reduced PPCs and length of hospital stay. PPCs, including pneumonia, were reduced by over 50% in patients at high risk of developing pulmonary complications [13]. In abdominal surgery beneficiary effects are reported on the incidence of atelectasis [16].

While in some surgical centers IMT is already used in the preoperative phase in patients undergoing esophageal resection, the effect of this intervention has not yet been investigated in a randomized controlled study in large surgical populations other than cardiac surgery. One non-randomized pilot study concluded that IMT is feasible and well tolerated before esophageal resection but did not show an effect on postoperative pulmonary outcome or length of hospital stay [15].

This article provides a detailed description of the background, the targeted population, and study methodology of the PREPARE study (preoperative inspiratory muscle training to prevent postoperative pneumonia in patients undergoing esophageal resection), a multicenter RCT investigating the effect of preoperative IMT in esophageal resection candidates.

## Methods/Design

### Study objectives

The primary objective is to evaluate the effect of preoperative IMT in addition to usual care, compared to usual care without IMT, in patients undergoing esophageal resection on the incidence of postoperative pneumonia. Secondary objectives are to evaluate the effect of preoperative inspiratory muscle training on length of hospital stay, duration of mechanical ventilation, incidence of other postoperative (pulmonary) complications, quality of life, and on postoperative respiratory muscle function and lung function.

### Study design and setting

This study is conducted as a single-blind multicenter RCT and will be coordinated by the University Medical Center Utrecht (UMCU) (Department of Rehabilitation, Nursing Science & Sports and Department of Surgery). Patients are randomly assigned to either care as usual without IMT or to IMT as an addition to care as usual. The randomization procedure is performed by a flexible web-based randomization system. The assignment sequence will be concealed. Randomization is stratified by center and minimization techniques are applied for surgical technique (transhiatal esophageal resection, transthoracic esophageal resection, minimally invasive esophageal resection).

This study is funded by ‘NutsOhra Foundation’ and ‘The Friends of the UMC Utrecht Foundation’ , and will be conducted in accordance with the principles of the Declaration of Helsinki and Good Clinical Practice Guidelines. The independent ethics committee of the UMCU has approved the study. Written informed consent will be obtained from all participating patients.

### Study population

All patients diagnosed with esophageal cancer and scheduled for esophageal resection with gastric conduit reconstruction by either a transhiatal esophageal resection (THE), a transthoracic esophageal resection (TTE), or minimally invasive (robot-assisted or conventional) thoraco-laparoscopic esophageal resection (MIE) are considered eligible for inclusion.

Further inclusion criteria are: (1) the patient is (cognitively) capable to understand and perform a preoperative IMT program; (2) the operation is scheduled at least 2 weeks after signing informed consent, since the patients need to be able to follow the intervention program for at least 2 weeks; and (3) the patient is willing to sign the informed consent form.

Patient are excluded based on the following criteria: (1) the patient is unable to communicate in the Dutch language; (2) age <18 years; and (3) the patient is participating in a conflicting trial concerning esophageal resection.

### Recruitment and informed consent

Patients are recruited from eight esophageal resection hospitals (in The Netherlands: Atrium Medical Center Heerlen, Canisius Wilhelmina Hospital Nijmegen, Reinier de Graaf Group Delft, University Medical Center Utrecht, VU Medical Center Amsterdam, Hospital Group Twente Almelo; in Belgium: University Hospital Gasthuisberg Leuven; and in Ireland: St. James’s Hospital Dublin). In every participating center one oncological surgeon and one physical therapist (PT) are the contact people for the coordinating researcher. Inclusion takes place for a period of approximately 1 year (September 2013 to August 2014). The local oncological surgeon determines whether a patient is eligible for inclusion in the PREPARE trial based on the inclusion criteria. At the start of the chemoradiation period or at the time the patient is informed about the planned surgery (when chemoradiation is not indicated), the surgeon informs the patient about the trial and hands over the trial information letter. After at least 5 days the patient is contacted by phone. When the patient is motivated to participate, an appointment with the local assessor is scheduled (after the chemoradiation period) for signing the informed consent form and completing the baseline measurements. The baseline measurement is followed by randomization, and the IMT instruction for patients in the intervention group. Both performed by the involved PT.

### Baseline assessment and follow-up measurements

The patient characteristics age, weight, height, gender, daily work, highest education, civil status, and preoperative physical therapy guidance (outside trial context) are prospectively recorded by means of a standardized interview during the baseline assessment. Data obtained from the patients’ medical records include history of COPD, smoking, pneumonia, diabetes mellitus, productive cough and cardiac events, tumor location, neoadjuvant treatment, prophylactic antibiotics, American Society of Anesthesiologists (ASA) score, admission and discharges dates, operation technique.

To evaluate the effect of IMT on respiratory muscle function and lung function, participants undergo measurements at five time points (baseline (T0), the day before surgery (T1), and during hospital stay on postoperative day 3 (T2), day 6 (T3), and day 9 (T4)). To determine an effect of IMT on quality of life (QoL) the EuroQol-5D and the SF-12 are assessed at baseline and 4 weeks after surgery. See for detailed description the paragraph secondary endpoints.

### Usual care

Surgical usual care in all Dutch centers consists of 5 to 6 weeks of preoperative chemoradiotherapy according to the CROSS group protocol [2]. In the centers in Belgium and Ireland, a different chemoradiotherapy schedule is used which is indicated on the tumor stage. The chemoradiotherapy schedule is followed by a recovery period of 4 to 8 weeks, depending on the recovery of the patient and waiting time for surgery per center. Patients not receiving chemoradiotherapy, will be placed on a waiting list for surgery which is in general at least 4 weeks. Physical therapy usual care in the preoperative phase can consist of ‘a preoperative instruction about postoperative physical therapy involvement’ , ‘preoperative advice to stay active or seek training guidance’ , ‘preoperative exercise guidance’ , or ‘no involvement until surgery’. Centers where preoperative IMT is currently part of usual care for all or a selected group of patients adapt to the PREPARE protocol and release IMT from their usual care. Patients assigned to the control group will only receive usual care.

Postoperatively physical therapy involvement can consist of respiratory physical therapy and physical therapy to facilitate early mobilization and independent functioning in activities of daily living. The differences in usual care per center is carefully registered.

### Intervention

Patients included in the intervention group receive an IMT program as an addition to usual care, starting in the recovery period after chemoradiotherapy. Patients not receiving chemoradiotherapy, start with the IMT program during the waiting period before surgery. IMT instructions are given by a specially instructed PT. The intervention used in this study entails the use of a tapered flow resistive inspiratory loading device: the POWERbreathe K3-series, an electronic IMT, and monitoring system [17]. It allows storing the data of the unsupervised training sessions to control compliance with the treatment.

The IMT intervention is based on the protocol of Bailey et al. [18]. This protocol is tailored individually. Starting inspiratory load is aimed at 60% of the measured maximal inspiratory pressure (Pi_max_). The load is incrementally increased based on the rate of perceived exertion (RPE) scored on a scale from 0 to 10 which is scored by the patient after each training session [19,20]. When patients score an RPE below 7, the inspiratory load of the threshold device will be increased with 5% by the patient. Patients have to complete 30 dynamic inspiratory efforts twice daily.

All patients in the intervention group are instructed during a face-to-face instruction session, will train at home 7 days a week for at least 2 weeks and continue training until surgery. Additionally, patients receive an instruction movie to watch at home and a training diary where the use of the inspiratory muscle trainer is illustrated step by step. Training results (RPE, level, load, power, volume, t-index) are recorded by the patients in the training diary after each training session. After the instruction session, the PT contacts the patient by phone after 3 days. When the training is not performed as instructed, the PT makes a follow-up appointment with the patient to repeat the instruction. Subsequently, training progress is evaluated during a weekly telephone consultation by the PT until surgery. At the end of the training period, IMT will be evaluated with a questionnaire. All involved PTs guiding patients during the IMT period received education and training during a meeting on the theory and practice of IMT organized by the research group.

### Blinding

The PREPARE study is a single blind randomized controlled trial. The local assessors (performing the informed consent procedure and the baseline and follow-up measurements), the surgeons, and other medical staff are blinded for group allocation. The patient and the PT (performing the randomization and guiding the intervention group) are not blinded for group allocation.

Patients in both groups will be informed that the PREPARE study aims to investigate the effect of a preoperative (home-based) IMT program on the reduction of postoperative pneumonia. The intervention group additionally receives detailed information about the intervention like timing, frequency, and intensity of the training. Included patients will not have contact with each other within the context of this trial.

### Primary endpoint

The primary outcome of the study is the incidence of postoperative pneumonia, as this is the most frequently occurring complication after esophageal resection and is an important cause of increased morbidity and mortality [6,21]. Pneumonia is defined according to the definition of the Utrecht Pneumonia Scoring System (UPSS) [22]. The UPSS corresponds with the clinical practice procedures for diagnosing pneumonia. Temperature, leukocyte count, and chest radiography are determinants that can objectively be assessed to diagnose pneumonia.

A score of 2 points or more (with at least 1 point assigned based on radiography) indicates treatment for pneumonia [22]. The UPSS variables will be scored in the participating centers on each day a pulmonary radiography has been performed. At the end of the trial, all chest radiographs will be reassessed by one blinded and independent radiologist. These scores will be used to determine the diagnosis of pneumonia in the context of this trial (Table 1).

**Table 1 T1:** **The Utrecht Pneumonia scoring system**[22]

**Diagnostic determinant**	**Values**	**Score**
Temperature (°C)	≥ 36.1 and ≤ 38.4	0
	≥ 38.5 and ≤ 38.9	1
	≥ 39.0 and ≤ 36.0	2
Leukocyte count [×10^9^/L]	≥ 4.0 and ≤ 11.0	0
	< 4.0 or > 11.0	1
Pulmonary radiography	No infiltrate	0
	Diffused (or patchy) infiltrate	1
	Well-circumscribed infiltrate	2

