### Sample size calculation

Sample size is calculated based on an expected reduction of 50% on the incidence of postoperative pneumonia [13]. Assuming a 30% incidence of postoperative pneumonia after esophageal resection in the control arm and using a significance level of 0.05 and a power of 80%, 118 patients are required in each arm [2,15,23]. Taking into account a 5% in-hospital mortality rate after surgery, approximately 124 patients per arm need to be included (248 patients in total).

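### The 2-point temperature band in the primary-endpoint score (Table 1) is joined by 'and', so no temperature can meet it; 'or' was evidently meant and the cell should be corrected

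*Protocol article*

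**What the plan says.** The primary outcome is the incidence of postoperative pneumonia, defined by the Utrecht Pneumonia Scoring System, for which the article cites a source and prints the score as Table 1 (Methods/Design, Primary endpoint). The decision rule is: "A score of 2 points or more (with at least 1 point assigned based on radiography) indicates treatment for pneumonia".

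The temperature rows of Table 1 are:

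- 0 points: "≥ 36.1 and ≤ 38.4"
- 1 point: "≥ 38.5 and ≤ 38.9"
- 2 points: "≥ 39.0 and ≤ 36.0"

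The leukocyte row gives 0 points for counts from 4.0 to 11.0 and 1 point for counts below 4.0 or above 11.0 (×10^9^/L). Radiography gives 0, 1 or 2 points for no infiltrate, a diffuse or patchy infiltrate, and a well-circumscribed infiltrate.

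The participating centers score the variables on each day with a chest radiograph. One blinded radiologist reassesses all radiographs at the end of the trial, and the section states that the scores decide the trial diagnosis. No other section repeats or corrects the temperature bands.

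**The concern.** A primary-endpoint rule should be executable as written. Here one cell is not: its two conditions exclude each other, and the temperatures it was meant to catch fall outside the other two bands as well. They are therefore left without any score.

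The scoring is done at eight centers (Recruitment and informed consent), and the central reassessment described covers radiographs only, so it would not detect a mis-scored temperature. If a scoring form or derivation program copied the cell literally, a high fever or a low temperature might be scored as 0 or set to missing. In the second case the imputation of missing measurements planned under Statistical analyses could replace a value that was in fact recorded. Recruitment had been open since September 2013 (Trial status), so scored days may already exist.

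**Working it through.** **Inputs.** Temperature, leukocyte and radiography bands and the 2-point rule: Table 1 and the text under Primary endpoint. Control rate 30%, relative reduction 50%, 80% power, 118 and 124 per arm: Sample size calculation. Two-sided 0.05: Statistical analyses. The temperature range 34.0 to 42.0 °C in steps of 0.1 °C is my assumption.

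**Step 1: the plan's own figure.** With 30% versus 15%, the unpooled two-proportion formula is n = (z~0.975~ + z~0.80~)² × [p₁(1 − p₁) + p₂(1 − p₂)] / (p₁ − p₂)². Here (1.960 + 0.842)² ≈ 7.849, the bracket is 0.21 + 0.1275 = 0.3375, and the denominator is 0.15² = 0.0225. So n = 7.849 × 0.3375 / 0.0225 = 117.7, or 118 per arm. The allowance 118 × 1.05 = 123.9 gives 124. The stated figures reproduce, and Table 1 does not enter them.

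**Step 2: coverage of the temperature bands.** The range holds 81 values.

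- 36.1 to 38.4 °C: 24 values, 0 points.
- 38.5 to 38.9 °C: 5 values, 1 point.
- At least 39.0 and at most 36.0 °C: no value.
- Matching no row: 34.0 to 36.0 °C (21 values) and 39.0 to 42.0 °C (31 values), together 52 of 81.

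With 'or' in the third row, each of the 81 values falls in exactly one band. The count of 52 describes the printed rule over an assumed range. It is not a proportion of patients.

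**Step 3: effect on the classification.** As printed, the total for an unmatched temperature is undefined. To see what could change, suppose it is counted as 0, and compare with the 2 points that 'or' would give. Pneumonia requires a total of at least 2 and at least 1 radiography point.

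| Radiography | Leukocytes | Total, unmatched = 0 | Total with 'or' | Pneumonia? |
|---|---|---|---|---|
| 0 | 0 | 0 | 2 | no / no |
| 0 | 1 | 1 | 3 | no / no |
| **1** | **0** | **1** | **3** | **no / yes** |
| 1 | 1 | 2 | 4 | yes / yes |
| 2 | 0 | 2 | 4 | yes / yes |
| 2 | 1 | 3 | 5 | yes / yes |

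Only one of six combinations changes: a diffuse or patchy infiltrate with a normal leukocyte count. An example is such a patient at 39.2 °C.

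**The case against.** The strongest reply is that this is one wrong conjunction whose meaning nobody would mistake. The 0-point and 1-point bands cover 36.1 to 38.9 °C without a gap at 0.1 °C steps, and the two cut-offs in the 2-point row are exactly those that bound what is left. The leukocyte row writes the same kind of two-sided range with 'or'. The score is also defined in a cited source, so Table 1 is not its only statement. All of this stands. It makes the intended reading evident, but it does not make the printed row correct.

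A reader might infer that pneumonia cases are being misclassified in this trial. The documents do not support that. The scoring forms and the derivation program are not shown, and nothing indicates that they repeat the slip. Even if they did, a change on one day need not change the patient's status, because scoring is repeated on every radiograph day.

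A reader might also infer a loss of power. Any such figure is driven by the share of events assumed to depend on this cell. Scaling both event rates down by an assumed 1%, 2%, 5% or 10% takes exact power at 118 per arm from 0.798 to 0.793, 0.788, 0.772 or 0.744. At 124 per arm, the 5% and 10% reductions give 0.795 and 0.768. The documents give no share, so none of these values is a finding.

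**Conclusion.** The point holds as an error in the text of the primary-endpoint rule: the 2-point temperature band is empty as printed, and extreme temperatures have no valid score. This needs no assumption. It deserves correction because it sits in the decision rule for the primary outcome rather than in background text.

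The possible effect is limited. It arises only if the printed row was applied literally, and then, with unmatched temperatures counted as 0, only on days with a diffuse or patchy infiltrate, a normal leukocyte count and an extreme temperature. How often that occurs cannot be derived from the documents. The sample size of 118, or 124 after the allowance, is unaffected.

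**What to change.** Check the row against the cited scoring system and correct the conjunction in the 2-point temperature band of Table 1. Confirm that the scoring forms at the centers and the program that derives the primary endpoint use the corrected band. Re-score days already entered only if that check finds that the error was carried over. In that case, review the days with a diffuse or patchy infiltrate, a normal leukocyte count and a temperature of at least 39.0 °C or at most 36.0 °C, plus any day whose total was set to missing because the temperature matched no row.

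The cost is one table cell and one check of the forms and program. Neither the design nor the sample size changes.
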